##### Secondary outcomes

**Students**

Mental health will be self-reported in questionnaires. Health-related quality of life will be measured with the questionnaire Kidscreen-10 [36], stress with the single item stress question (SISQ) [37], psychosomatic health problems with the Psychosomatic Problem Scale (PSP), and self-esteem with the Rosenberg Self-Esteem Scale (RSES) [38].

Physical activity and sedentary time will be measured with accelerometry, which is an objective way of assessing detailed physical activity patterns [39]. For seven consecutive days, physical activity patterns will be measured with triaxial accelerometers (model GT3X+, Actigraph, LCC, Pensacola, USA). Participants will be instructed to wear the accelerometer on their right hip during all hours when awake except during activities involving water. The accelerometers will be sent back to the researchers in pre-paid envelopes. The software ActiLife Data Analysis, will be used to process the accelerometer data. Uniaxial (vertical axis) data will be saved in 5-second epochs. Non-wear time will be defined as 60 min of 0 counts, with no spike tolerance. A filter will be applied to distinguish school-time physical activity from leisure-time activity, based on school schedules for each class. A valid day is defined as having at least 500 min of activity registration per day, and a minimum of 3 days, including at least one weekend day, will be considered a valid week. School time will be considered valid if there are at least two valid weekdays. Sleep time will be based on the self-reported questions. The physical activity outcomes will be time spent in sedentary, light physical activity (LIPA), and moderate to vigorous intensity (MVPA). The counts from the accelerometer data will be categorised into minutes spent in: sedentary intensity (0–100 counts/minute), LIPA (101–2295 counts/minute), and MVPA (≥ 2296 counts per minute) [40].School time will be determined using the start and end times of each school day, as extracted from the school schedules. The weekly average of ≥ 60 min of MVPA per day will be used to reach the physical activity recommendation, based on both school and leisure time. In sensitivity analyses, activity intensity will be divided into 25 categories for high resolution analysis. In these analyses, the innate low-pass filter at 1.63 Hz will be removed and replaced with a 4 Hz cut-off for better validity [41].

Cognitive function will be assessed using a computer-based test battery measuring working memory (letter updating), episodic memory (word recall), and perceptual speed (number comparison). Using three different domains of cognitive function and multiple trials allows for a broader understanding of cognitive function and increases the reliability of the test while keeping participant burden to a minimum. This design also allows for the construction of a latent variable for cognitive function. A previous study has shown a version of this test battery to be a valid and robust measure of these cognitive abilities in an older population [42].

Academic performance in Swedish, English, and mathematics will be measured by grades and standardised Swedish national tests collected from the Statistics Sweden (SCB) register (grade 9) and directly from the schools (grades 7 and 8).

Body mass (kg) and height (cm) will be measured in duplicates using standardised procedures with SECA instruments. Body Mass Index (BMI) will be calculated as body mass (kg) divided by height (m) squared. Overweight and obesity will be defined according to the International Obesity Task Force standard deviation score (BMI sds), computed according to a Swedish reference standard [43].

Health behaviours will self-reported in a questionnaire. Physical activity and sedentary behaviours include questions about transport to and from school, physical education attendance, participation in organised sports/activities, and screen time use. Dietary intake will be assessed by self-report in a questionnaire, based on a composite score of indicator foods, including healthy foods (fruit and vegetables), unhealthy foods (sweets and ice cream), and sugar-sweetened beverages.

Sleep will be measured and expressed as total sleep time and efficiency using a questionnaire where the participants report when they usually go to bed and wake up.

Motivation to physical activity will be measured using an adapted version of the Behavioural Regulation In Exercise Questionnaire (BREQ) [32].

Functional disabilities will be self-reported using the Modified Child Functioning Module [44].

Background characteristics: Parental educational level will be collected from the SCB register as an indicator of socioeconomic status. The highest level of education attained in the household will be used and dichotomised into low education (≤ 12 years) and high education (> 12 years). Parental country of birth will be self-reported in a questionnaire. Information about school type (independent or public) will be collected from the National Agency for Education.

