### Intervention components

This multi-component intervention will be performed during an extended school day, 60 min three times per week, for six months and include three components described below. The intervention activities will be included as part of the mandatory school curriculum for all the students in the intervention schools.Different types of physical activities (1 × 60 min per week). The physical activities will be chosen in collaboration with teachers and students, and will take place in both indoor school facilities and outdoor areas. Examples of activities are swimming, dancing, gym, circuit training and ball sports, to suit all interests.Homework support with short activity breaks, 3–5 min every 30 min (1 × 60 min per week).Walking and listening to an audiobook (1 × 60 min per week), in areas nearby the school.

To make the programme integrated and sustainable, the activities can be scheduled at any time during the school day and will be led by school staff.

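### School-time accelerometer data are accepted on whole-day wear, with no minimum wear during scheduled school hours

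*Protocol article*

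**What the plan says.** All the rules are in the Students part of the Secondary outcomes section of the protocol article.

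- Day validity: "A valid day is defined as having at least 500 min of activity registration per day". The registration may fall anywhere in the day.
- School-time validity: "School time will be considered valid if there are at least two valid weekdays".
- School window: "School time will be determined using the start and end times of each school day, as extracted from the school schedules".
- Non-wear: "Non-wear time will be defined as 60 min of 0 counts, with no spike tolerance".
- Outcome scale: minutes in sedentary, light and moderate-to-vigorous intensity. Scaling to wear time is not mentioned.
- Wear instruction: students are to "wear the accelerometer on their right hip during all hours when awake except during activities involving water", so wear before and after school counts towards the 500 min.

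No other section adds a wear requirement inside the school window.

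**The concern.** The school window is cut out of the day using class schedules, but whether a student's data in that window are usable is decided on the whole day. A student can meet the daily threshold largely from mornings and evenings, have little recorded at school, and still contribute a school-time value that is treated as complete.

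Minutes in school time are the most direct measured sign that the programme raised activity during the school day. The Background says earlier school programmes generally failed to do this. If school minutes are lost to non-wear, that measure becomes noisier and is shifted downwards. The multiple imputation planned under Data analysis does not repair this, because these values are declared valid and are not missing.

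**Working it through.** The article derives no figure from this rule, so there is none to reproduce. The check asks how much school non-wear the rule lets through and what that does to a school-time mean.

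**Inputs.** From the article: 500 min per valid day, two valid weekdays, non-wear as 60 min of zero counts. Not in the article, so assumed: waking day W and school day S.

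**Step 1: non-wear allowed on a valid day** = W − 500.

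- W = 14 h: 840 − 500 = 340 min
- W = 15 h: 900 − 500 = 400 min
- W = 16 h: 960 − 500 = 460 min

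**Step 2: partial school non-wear.** Take a school day of 6 to 7 h (360 to 420 min). Half of it unworn is 180 to 210 min. That is below the smallest allowance of 340 min, so a half-worn school day passes at every assumed W, with at least 340 − 210 = 130 min to spare.

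**Step 3: the extreme.** The least school wear that the rule forces is max(0, 500 − (W − S)). Over a deliberately wide range, in minutes (share of the school day):

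| W | S = 5 h | S = 6 h | S = 7 h | S = 8 h |
|---|---|---|---|---|
| 14 h | 0 | 20 (6%) | 80 (19%) | 140 (29%) |
| 15 h | 0 | 0 | 20 (5%) | 80 (17%) |
| 16 h | 0 | 0 | 0 | 20 (4%) |
| 17 h | 0 | 0 | 0 | 0 |

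In 13 of the 16 cells, a day with 0 to 20 min of school wear can be valid. This needs heavy wear outside school: at W = 15 h and S = 6 h, 500 of the 540 out-of-school minutes (93%). Partial school wear is the likelier form.

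**Step 4: effect on the school-time mean.** Suppose recorded minutes are proportional to the shares f1 and f2 of school time worn on two valid weekdays. The recorded mean is then (f1 + f2)/2 of the true mean:

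- f1 = 1, f2 = 0.5: 75%
- f1 = 0.5, f2 = 0.5: 50%
- f1 = 1, f2 = 0: 50%
- f1 = 0.1, f2 = 0.1: 10%

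If the average share worn, f, is the same in both arms and unrelated to activity, a true difference between arms in minutes shrinks to f times its size.

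**Step 5: where the lost minutes go.** A run of 60 min or more of zeros is removed as non-wear and reduces every category, sedentary included. A shorter gap stays in as zero counts and falls in the sedentary band.

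**The case against.** The strongest reply is that students are told to wear the device throughout waking hours, that the article gives no school hours, waking hours or rate of poor school wear, and that the effect on minutes depends on not adjusting for wear. The article says a data analysis plan was submitted with the registration, and that plan may scale to wear time. This limits the size of the point. If outcomes are scaled, the downward shift largely goes. What remains is that a value resting on a small slice of the school day is still accepted. The validity rule itself is stated in the article, so it has not been left to another document.

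Four stronger readings are tempting, and the documents do not support them.

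- **A student who puts the device on only after school passes.** Mostly not. With 60 min awake before school (assumed), after-school time is W − S − 60. For W = 14 to 16 h and S = 6 to 7 h it reaches 500 min only near the top of the waking range: at W = 960 min, for S of 400 min or less. At W = 840 or 900 min it never does.
- **Non-wear is scored as inactivity.** Long gaps are excluded by the non-wear rule. Only gaps under 60 min enter the sedentary band.
- **Swimming biases one arm.** Swimming is one of several example activities chosen locally. The Data collection section places outcome measurement before and after the intervention, so the documents do not show that sessions run in the accelerometer week. Nothing says control students have no water activities at school. Nor is the validity rule the cause: a 60-min removal leaves 300/360 = 83% or 360/420 = 86% worn, which a 75% school-hours rule would still pass.
- **The weekly average dilutes a weekday effect to a third.** The valid-week rule does admit one weekday with two weekend days, but that figure assumes a simple mean over valid days, which the article does not state.

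**Conclusion.** The point holds as a modest defect in a secondary outcome. The stated school-time rule tests wear over the whole day when the quantity analysed is confined to school hours. Under assumed waking days of 14 to 16 h, it allows 340 to 460 unworn minutes on a valid day, enough to cover half of a 6 to 7 h school day at every assumed value and nearly all of it in some cases. The result is added noise and, for unscaled minutes, understated school-time activity. The 75% and 50% figures illustrate particular wear patterns; they do not estimate the bias in this trial, because the frequency of school non-wear is unknown. No difference between arms is established. The primary outcome and the sample size are not affected. The change is worth making because it is cheap.

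**What to change.** In the Students part of Secondary outcomes, replace the school-time rule:

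1. Count a weekday towards school time only if the device was worn for a stated share of that day's scheduled school minutes, for example at least 75%.
2. Require at least two such weekdays.
3. Repeat the analysis with a lower and a higher threshold, for example 60% and 90%.
4. Express school-time outcomes relative to school wear time, for example minutes per hour worn. If the school day is longer in intervention schools, state whether the target is the rate or the total over the scheduled day; the rate times scheduled length gives the total.

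Optionally, state how the weekly average is formed and weight weekday and weekend means 5:2, so that weekdays carry their calendar share of 5/7 = 0.71.

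The cost is a processing step on time-stamped counts and class schedules that the plan already uses. The downside is that some students lose a valid school-time value; report how many, by arm and threshold.

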### Control group

The control group will have unchanged school schedules and will be offered the intervention after the post-intervention measurements in the following school year.

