## Discussion

Increasing health inequalities, declining physical activity and fitness, and an increase in mental health problems among adolescents require in-depth knowledge and new strategies for preventive work. This theory-driven, multi-component school-based intervention addresses a critical knowledge gap in how to effectively promote mental well-being, physical activity, and academic performance among adolescents. Although schools are increasingly recognised as key settings for health promotion, there is still limited evidence on how to design and implement integrated programmes that are both evidence-based and feasible within existing school structures. By integrating physical activity and homework support within an extended school day, this novel project has the potential to sustainably improve adolescent health and learning.

The intervention combines physical activity and homework support, scheduled within an extended school day, and is designed to be integrated into existing school structures and routines. By taking place during regular school hours and being delivered by school staff, the programme may help overcome common barriers such as time constraints and limited capacity for additional initiatives. This design is expected to enhance the feasibility of implementation and increase the likelihood of long-term sustainability, thereby contributing to improvements in adolescent health and academic achievement. To ensure fidelity and quality, school staff receive ongoing support throughout the intervention period.

A thorough process evaluation is a crucial part of intervention evaluation, as it provides a contextual understanding of both how the intervention is delivered and the resulting outcomes. Understanding each component and the delivery process is essential to clarify the mechanisms and contextual factors influencing the effectiveness of the intervention. Therefore, there is a need to examine all aspects of a programme, especially in complex multi-component interventions, as we have intended to do in this intervention.

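### If the intervention lengthens the school day, the school-time accelerometer window depends on arm, so school and leisure contrasts mix real change with time moved across the boundary

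*Protocol article*

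**What the plan says.** **Outcome definition.** Secondary outcomes (Students) splits the accelerometer record by timetable: "A filter will be applied to distinguish school-time physical activity from leisure-time activity, based on school schedules for each class". The boundary is fixed as follows: "School time will be determined using the start and end times of each school day, as extracted from the school schedules". The scale is absolute time: "The physical activity outcomes will be time spent in sedentary, light physical activity (LIPA), and moderate to vigorous intensity (MVPA"), with counts classified into minutes per intensity band. School time has its own validity rule (two valid weekdays). The recommendation outcome pools school and leisure time.

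**Timetables.** Intervention components says: "This multi-component intervention will be performed during an extended school day, 60 min three times per week, for six months". The sessions are compulsory for all students in intervention schools, and "the activities can be scheduled at any time during the school day". Under Control group: "The control group will have unchanged school schedules". The Discussion describes the programme in a different way, "By taking place during regular school hours and being delivered by school staff", although the same section also places it in an extended day and later argues against loading the existing mandatory hours.

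**Timing and model.** Data collection places measurements on either side of the intervention period. It does not say whether the longer timetable still applies in the post-intervention accelerometer week. Data analysis names group and the baseline value of the outcome, then adds gender and parental education.

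**The concern.** Read together, these rules let allocation set the measuring window. A longer day in one arm moves clock time from leisure to school in that arm, whatever the students do in it. The lengthening starts after baseline, so the baseline value carries no information about it and adjusting for that value leaves it in place.

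The risk lies in how the splits are read. School-time sedentary, light and MVPA minutes could all be higher in the intervention arm, and the leisure counterparts all lower, partly because the boundary moved. The first pattern could be reported as more activity, or more sitting, at school. The second could be reported as compensation in leisure time. The Background says that school programmes have failed to raise children's activity, so readers are likely to look at the school-time result.

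**Working it through.** The plan gives no figure for this effect, so there is none to reproduce. The check is direct arithmetic.

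**Inputs from the article**
- Sessions: 3 per week, 60 min each (Intervention components).
- Control timetable: 0 min added (Control group).
- 27 schools per arm with 50 students each (Sample size calculation).

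**Assumptions, not in the article**
- Five school days a week.
- Composition of the moved time, with identical behaviour in both arms: sedentary 55-80%, light 15-35%, MVPA 3-10%.
- For scale only: SD of school-time MVPA 8-12 min/day, ICC 0.02-0.10.

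**Step 1: shift of the window.** Minutes added per week / 5:
- all three sessions extend the day: 180 / 5 = 36 min per school day
- two do: 120 / 5 = 24
- one does: 60 / 5 = 12
- none does, or the longer timetable has ended by the measurement week: 0

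**Step 2: minutes reclassified with no change in behaviour.** Shift x share of the moved time, in min per school day:

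| Shift | Sedentary | Light | MVPA |
|---|---|---|---|
| 36 | 19.8-28.8 | 5.4-12.6 | 1.1-3.6 |
| 24 | 13.2-19.2 | 3.6-8.4 | 0.7-2.4 |
| 12 | 6.6-9.6 | 1.8-4.2 | 0.4-1.2 |

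School time gains these amounts, leisure time loses the same amounts, and the whole-day difference is 0.

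**Step 3: scale.** With 27 x 50 = 1,350 students per arm, SE = SD x sqrt(2 x (1 + 49 x ICC) / 1350), and the difference detectable at 80% power is about 2.8 x SE.
- SD 8, ICC 0.02: SE 0.43, detectable 1.2 min/day.
- SD 12, ICC 0.10: SE 1.12, detectable 3.1 min/day.

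This ignores attrition and the gain from baseline adjustment. At the full 36-minute shift, the reclassified MVPA (1.1-3.6) is of the same order as the detectable difference.

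**Step 4: an example without assumed intensity shares.** Homework support has breaks of 3-5 min every 30 min. A 60-minute session therefore holds 60 - 2 x 5 = 50 to 60 - 2 x 3 = 54 min of homework, or 10.0-10.8 min per school day averaged over five days. If that work is done seated, it counts as school sedentary time when it falls in the added hour. The same homework done at home by a control student counts as leisure.

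**Step 5: after the change.** With the same clock window in both arms, identical behaviour gives a difference of 0 for school and for leisure. A share of window time removes the effect of length. It does not remove a difference in activity mix between the added time and the rest of the day.

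**The case against.** The strongest reply is that the added time is the intervention. Activity that school now provides is a real effect on school-time activity, and less leisure activity is real displacement. Two of the three sessions are active by design, so identical behaviour is a hypothetical. This stands in part: a school-time difference would not be pure artefact. But raw minutes in an arm-dependent window cannot show how much is new activity and how much is the same activity under another label.

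Second, free placement of sessions, and the Discussion's reference to regular hours, mean the day may not be longer everywhere. This also stands in part. Sessions fitted into existing gaps need not move the start or end of the day, so 36 min is an upper bound. Where the day is longer in total, placement does not help, because the window runs from its start to its end.

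Third, the article does not say outright that school and leisure minutes will be compared between arms, and the headline outcomes can be read as whole-day. That is fair. Still, the filter and the separate school-time validity rule have little purpose unless the splits are reported.

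A reader might also infer that the lack of a wear-time or window-length term in the models is itself an error. The article does not support that. It refers to an analysis plan submitted with the registration, which is not shown and may cover such terms. The point rests on the window definition that the article does fix. Adjusting for whole-day wear time would not help in any case, because moving the boundary leaves whole-day wear unchanged.

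**Conclusion.** The point holds in conditional form. School time is tied to each class's timetable, and the plan describes a timetable that changes in one arm only. If the day is truly longer and the longer timetable applies in the post-intervention accelerometer week, up to 36 min per school day passes from leisure to school in the intervention arm (12 or 24 min under partial extension). The MVPA and sedentary figures in the working also rest on assumed intensity shares.

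A reader might infer that the trial's physical activity results as a whole are biased, or that any school-time gain would be spurious. The documents support neither. Whole-day minutes and the recommendation outcome do not depend on where the boundary lies, and the primary outcome, anxiety, is untouched. The weakness is confined to interpreting the school and leisure splits within one family of secondary outcomes. It is worth correcting because the correction is cheap.

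**What to change.** 1. For between-arm comparison of the splits, use one common clock window per school or class in both arms at both time points. This could be the pre-intervention timetable with the added time reported separately, or a fixed window that covers the extended day.
2. Report the share of valid wear time within that window as a supporting analysis only, since it removes just the length effect.
3. Name whole-day MVPA and whole-day sedentary time as the lead accelerometer contrasts.
4. State whether the extended timetable is in force during the post-intervention accelerometer week.
5. Reconcile Intervention components with the Discussion on extended versus regular hours, and record for each intervention school how far the day was actually lengthened.

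The cost is some reprocessing of accelerometer files and a few sentences of text; no new data collection from students is needed. The common window follows each class's actual timetable less closely. A window wide enough for the extended day counts some after-school time as school time for controls, whereas the pre-intervention window leaves the added time to be described on its own.
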